#### Treatment variables

Data will also be collected on the number of completed modules, dropouts of treatment, sent messages, and therapist time spent in the digital platform for each participant and any additional time needed, for example, phone calls outside the platform. A treatment completer is defined as a participant who completed all treatment modules or responded early. Early recovery is defined as the participant showing a positive response after completing at least 3 modules, with a minimum of a 10-point reduction on the PCL-5 or achieving a total sum score below 30, and both the participant and therapist agreeing to conclude the treatment. Participants who discontinue treatment or experience early recovery will be encouraged to continue their participation in the remaining outcome assessment points.

Ratings on the subjective units of distress (SUD) will be collected during exposure exercises (pre, during, post and maximum), and harm expectancies will be assessed using digital worksheets. The Credibility/Expectancy Questionnaire (CEQ; [22]) and Working Alliance Inventory–Short Form Revised (WAI; [23]) will be utilized to assess treatment credibility and working alliance between the treatment arms.

### Participant timeline {13}

The participant timeline and timepoints for assessment for the study can be seen below in Table 2.

**Table 2 Tab2:** Participant timeline and timepoints for assessment

	Enrollment	Allocation	Baseline	Weeks 1–10	1-months follow up (primary end-point)	6-month follow-up	12-month follow-up
**Enrollment:**							
Eligibility screen	X						
Informed consent	X						
Allocation		X					
Treatment:							
HOPE				X			
Control condition				X			
**Clinical administered instruments:**							
CAPS-5	X				X	X	X
**Self-rated instruments**							
PCL-5			X	X	X	X	X
ITQ			X		X	X	X
PHQ-9			X		X	X	X
EQ-5D			X		X	X	X
AQoL-6D			X		X	X	X
TIC-P			X		X	X	X
NEQ					X	X	X
CEQ*							
WAI-SR**							
SUD***				X			

*Abbreviations: AQoL-6D* Assessing Quality of Life 6 Dimensions, *CAPS-5 *Clinician-Administered PTSD Scale for DSM-5, *CEQ *Credibility/Expectancy Questionnaire, *ITQ *The International Trauma Questionnaire, *NEQ *Negative Effects Questionnaire, *SUD *Subjective Units of Distress Scale, *TIC-P *Treatment Inventory of Costs in Psychiatric Patients, *PHQ-9 *Patient Health Questionnaire, *WAI-SR *Working Alliance Inventory–Short Form Revised

*CEQ is administered after the first module in each treatment format

**WAI-SR is administered at start of the third treatment week in each treatment format

***SUD rating will only be collected in the HOPE group each time digital worksheets for exposure are filled in

Interested applicants can self-refer to the study through a dedicated secure website by completing an online screening battery comprising questions about inclusion and exclusion criteria, demographics, symptoms of PTSD and depression, and the Web Screening Questionnaire for common mental disorders (Donker et al., 2009) to assess for comorbidities. Written information about the study will be given before the screening, including objectives, benefits, risks, and requirements imposed by the study. The participants will be encouraged to download the study information and consent form to keep for future reference. Applicants will undergo a clinical psychiatric assessment interview, which includes the CAPS-5, to determine their eligibility for the study. If the inclusion criteria are met, the applicant will be invited to take part in the research (please see Table 1 for the specific inclusion and exclusion criteria). Decisions on inclusion will be made by the assessor and the principal investigator ([name]) together.

### Sample size {14}

A priori power analysis determined the sample size for comparing HOPE with an active control at the primary endpoint (1 month). Based on prior internet-delivered CBT work showing a between-group effect of Cohen’s *d* = 0.38 [8], we powered the trial to detect a conservative effect of *d* = 0.35 with 80% power at a two-sided *α* = 0.05 under 1:1 randomization. This yields *n* = 129 per group at the primary endpoint. To accommodate 10% data attrition (missing primary outcome), consistent with retention in other therapist-guided digital trials [11], we inflated the sample to *N* = 286 (143 per arm), expected to retain 129 per arm for analysis.

### Recruitment {15}

The study will recruit participants from a psychiatric outpatient clinic in Stockholm. Mental health professionals working at the clinic will have access to an information sheet of the study, which they can present and discuss with patients. Self-referrals are available through a dedicated website, and advertisements will be placed on social media with information about the study.

## Assignment of interventions: allocation

### Sequence generation {16a}

After eligibility confirmation and baseline assessment, participants will be randomized 1:1 to HOPE or the active control, stratified by self-rated complex PTSD (yes/no) and gender. The sequence is computer-generated with variable block sizes and programmed by an external unit (Karolinska Trial Alliance) via a secure, audited, web-based system independent of the clinical team. The sequence is stored server-side and inaccessible to site staff. Allocation is released only after baseline completion through role-based login, ensuring concealment; staff cannot foresee upcoming assignments. On randomization, the system issues a tamper-evident allocation certificate (participant ID, assigned arm, personnel ID, timestamp) and maintains a full audit trail.

### Concealment mechanism {16b}

The allocation sequence in the digital system is concealed from all study personnel.

### Implementation {16c}

The local project leader will assign participants to interventions.

## Assignment of interventions: Blinding

### Who will be blinded {17a}

Group allocation will be masked to the assessors up to completion of the 12-month follow-up. Participants will receive explicit instructions not to discuss their treatment allocation with the assessor. Following each assessment, the assessors will be requested to guess the participants’ allocation, and these responses will be compared to chance at the study’s conclusion to assess the integrity of blinding.

If participants inadvertently disclose the treatment allocation during the assessment, the assessment will stop, and another blind assessor will reassess the diagnosis. The participant will also be assigned another assessor at subsequent follow-ups. The primary outcome assessors and trial statistician will be blinded to group allocation during the whole duration of the trial.

### Procedure for unblinding if needed {17b}

Emergency unblinding will occur when clinically necessary, such as when treatment decisions require knowledge of the intervention or when an unexpected serious adverse event arises. Other instances of unblinding include (1) conducting interim analysis according to the study analysis plan and (2) at the conclusion of the study to assess the intervention’s effects.

## Data collection and management

### Plans for assessment and collection of outcomes {18a}

Participants will complete baseline assessments, weekly measures throughout the treatment period, immediately after treatment completion and at the 1-month, 6-month, and 12-month follow-ups. All data are collected in a secure digital platform (BASS).

### Plans to promote participant retention and complete follow-up {18b}

No reimbursement to participants will be given to complete the assessment. The digital platform sends out automatic reminders if assessments are late.

### Data management {19}

Case report form data will be imputed to a data file. All data will be handled and eventually archived according to Swedish and European legislation. Data will not be made publicly available. Participants will complete online questionnaires via BASS, a password-protected digital platform hosted by the Karolinska Institutes secure computing facilities, which also handle data backup. The platform also uses two-factor authenticating. Participants will complete assessments and interviews with researchers via phone or secure video-conferencing software used at the recruitment site.

### Confidentiality {27}

The data generated in the research project will be managed and stored according to Karolinska Institutet’s and Stockholm County’s Research Data Management Policy. The study personnel involved in the trial are bound by confidentiality principles in their role as employers in the health care system.

### Plans for collection, laboratory evaluation, and storage of biological specimens for genetic or molecular analysis in this trial/future use {33}

Not applicable since the trial does not involve collecting biological specimens for storage.

## Statistical methods

### Statistical methods for primary and secondary outcomes {20a}

The data analyses will be carried out by an independent statistician who is not part of the research group. This statistician will also remain blind to the group allocation throughout the duration of the trial. The intention-to-treat approach to the analysis population will be applied in all cases unless specified otherwise. The significance level for all statistical tests will be *α* = 0.05.

For our primary research questions, we will fit a linear mixed-effects model for repeated measures to evaluate change in CAPS-5 total scores within and between groups over time. Fixed effects will include treatment, time, and the treatment × time interaction; a participant-specific random intercept will be specified. An unstructured within-participant covariance will be used, allowing distinct correlations between all pairs of time points. The model will be estimated by restricted maximum likelihood and will use all available observations, yielding unbiased estimates under missing at random or missing completely at random assumptions. The primary hypothesis will be tested two-sided at *α* = 0.05. No adjustments will be made for multiplicity.

As a complementary check at the primary endpoint, we will fit a linear regression of change in CAPS-5 from baseline to 1-month on randomization arm, adjusting for baseline CAPS-5.

We will report within- and between-group effect size (Cohen’s *d*) with 95% CIs. Effects will be deemed statistically significant at *p* < 0.05. Magnitudes will also be described using conventional benchmarks: small (0.20), medium (0.50), large (≥ 0.80).

Crossover participants continue all scheduled outcome assessments. Post-crossover data are obtained as part of a naturalistic follow-up.

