#### Secondary outcomes and analyses

Unless stated otherwise, analyses mirror the primary modelling strategy: continuous outcomes will be analyzed with linear mixed-effects models using all available observations and yielding unbiased estimates under MAR/MCAR. Binary (and ordinal) outcomes will be analyzed with mixed-effects logistic (or cumulative-logit) models; cross-sectional categorical comparisons will use *χ*^2^ or Fisher’s exact tests as appropriate. Effect sizes will be reported as model-based standardized mean differences (Cohen’s *d*) for continuous outcomes and odds ratios for binary outcomes, each with 95% CIs. All secondary analyses are exploratory and *p*-values are nominal (no additional multiplicity adjustment).

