### Methods for additional analyses (e.g., subgroup analyses) {20b}

We will explore differences in treatment effects by gender in a subgroup analysis by including an interaction term between treatment arm and gender. Exploratory mediation will evaluate whether change in emotional responding, adherence, post-traumatic cognitions, avoidance, and alliance mediates treatment effects on CAPS-5. Moderation by baseline demographics and clinical history (e.g., PTSD/CPTSD severity, trauma type and timing, childhood adversity, comorbidity, perceived threat, education, employment, credibility/alliance) will be tested via treatment × covariate interactions; for prognostic models of CAPS-5 response, logistic regression will be used with model calibration assessed by Hosmer–Lemeshow and calibration plots.

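### Randomisation is stratified by complex PTSD and gender but the stated models include neither factor; if the factors are prognostic beyond baseline CAPS-5, inference is slightly conservative

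*Protocol article*

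**What the plan says.** Under Sequence generation {16a}, allocation is 1:1, "stratified by self-rated complex PTSD (yes/no) and gender", and "The sequence is computer-generated with variable block sizes".

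Under Statistical methods for primary and secondary outcomes {20a}, the primary analysis is a mixed model for CAPS-5 over time. The article specifies the random intercept, the covariance structure, the estimator and the fixed part: "Fixed effects will include treatment, time, and the treatment × time interaction". The complementary check regresses change in CAPS-5 to 1 month "on randomization arm, adjusting for baseline CAPS-5". Neither names a stratification factor.

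Under Secondary outcomes and analyses, the approach is carried over: "Unless stated otherwise, analyses mirror the primary modelling strategy".

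The two factors reappear only under Methods for additional analyses {20b}. Gender enters a subgroup analysis "by including an interaction term between treatment arm and gender", and complex PTSD is among the exploratory moderators: "Moderation by baseline demographics and clinical history (e.g., PTSD/CPTSD severity". Neither use puts the factors into the primary comparison.

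**The concern.** Blocked allocation within strata makes the arms more alike on complex PTSD and gender than simple randomisation would. If those factors predict the outcome, the treatment estimate varies less from trial to trial than a model without them assumes. The variance between strata then stays in the residual, the reported standard error is too large, the confidence interval is too wide, and the test rejects less often than its nominal level allows.

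What is at stake is precision that the design has already paid for. The error is on the safe side, but the sample size gives about 80% power with no allowance beyond 10% attrition, so precision that costs almost nothing is worth keeping.

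**Working it through.** **Inputs from the article.** Effect: "we powered the trial to detect a conservative effect of *d* = 0.35", with 80% power, two-sided α = 0.05, 1:1 allocation, 129 per group analysed (Sample size {14}). CAPS-5 is taken at enrolment and at 1, 6 and 12 months (Outcomes {12}, Table 2).

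**Step 1: the plan's own figure.** n per group = 2 × (1.960 + 0.842)² / 0.35² ≈ 128.2, rounded up to 129, as stated. With n = 129, SE = √(2/129) = 0.1245 in SD units, 0.35/0.1245 = 2.811, and power = Φ(2.811 − 1.960) = 80.3%. The t-test version gives 129.1 per group and 80.0% power at 129. The calculation is an unadjusted two-group comparison and takes no credit for any covariate.

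**Step 2: effect of omitting the factors.** Let R² be the share of outcome variance, not already removed by the model, that the two factors explain. The article gives no such figure, so a range is assumed. With strata balanced, the true SE is the unadjusted SE × √(1 − R²). The model without the factors reports the unadjusted SE, and the model with them reports the true one. Hence:

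- true type I error without the factors = 2 × [1 − Φ(1.960/√(1 − R²))]
- power without the factors = Φ((2.811 − 1.960)/√(1 − R²))
- power with the factors = Φ(2.811/√(1 − R²) − 1.960)

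For R² = 0.10, √0.90 = 0.9487. Type I error: 1.960/0.9487 = 2.066, giving 3.9%. Power without: 0.851/0.9487 = 0.897, giving 81.5%. Power with: 2.963 − 1.960 = 1.003, giving 84.2%.

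| Assumed R² | Reported SE too large by | True type I error | Power, omitted | Power, adjusted | Gain (points, before rounding) |
|---|---|---|---|---|---|
| 0 | 0% | 5.0% | 80.3% | 80.3% | 0 |
| 0.02 | 1.0% | 4.8% | 80.5% | 81.0% | 0.5 |
| 0.05 | 2.6% | 4.4% | 80.9% | 82.2% | 1.4 |
| 0.10 | 5.4% | 3.9% | 81.5% | 84.2% | 2.7 |
| 0.20 | 11.8% | 2.8% | 82.9% | 88.2% | 5.2 |

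**Step 3: how much of this reaches the stated models.** Both models already use baseline CAPS-5, one as a time point and the other as a covariate. A simulation with 258 participants, d = 0.35, stratified blocks of 4 and 6, and 4,000 runs per scenario compared each analysis with and without the factors. Assumed: 50% complex PTSD, a 20%/80% gender split, and a baseline–endpoint correlation of 0.5 within strata. The change-score analysis is the complete-data counterpart of the treatment × time contrast, and adding the factors to it corresponds to adding factor × time terms to the mixed model.

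| Factors explain | Baseline-adjusted regression, power without → with | Change contrast, power without → with |
|---|---|---|
| 10% of baseline, 10% of endpoint | 92.4% → 93.0% | 84.7% → 84.7% (SE 0.1180 both) |
| 20% of baseline, 10% of endpoint | 92.7% → 92.6% | 86.1% → 86.4% |
| 0% of baseline, 10% of endpoint | 89.7% → 92.2% | 79.3% → 82.3% |

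Only the difference within each cell bears on this point. The power levels depend on the assumed correlation and cannot be read against the planned 80%. The gain is 2.5 to 3.0 points where the factors say something about the endpoint that baseline does not, and close to nothing otherwise.

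**Step 4: what the terms cost.** Baseline is itself a time level in the mixed model. A factor entered only as a main effect shifts all visits equally and barely moves the treatment × time contrast, so time interactions are needed whether or not the 6- and 12-month visits are in the model. With four visits and two-level factors, that is 2 main effects + 2 × 3 interactions = 8 parameters.

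**The case against.** The strongest reply is that the harm is conditional. Nothing in the article shows that complex PTSD or gender predicts 1-month CAPS-5, or says why they were chosen as strata. Complex PTSD would plausibly act partly through baseline severity, which the models already use. This stands: it limits the size of the point and removes any certainty about the loss.

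A second reply is that the full analysis plan on OSF is not shown and that the article says the fixed effects will include these terms, not that they are the only ones. This has some weight. But the article specifies the model down to covariance structure, estimator and the single covariate of the check regression, and the list reads as complete. If the OSF plan already contains the factors, the article and that plan disagree and the article should be brought into line.

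A third reply is that the secondary analyses are labelled exploratory with nominal p-values, so the carry-over matters little. That is fair; carrying the terms over is for consistency.

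A reader might also set adjusted power against 80.3% throughout and read gains of 0.7, 1.9 and 3.9 points at R² of 2%, 5% and 10%. That is the wrong comparison. The smaller true standard error also raises the power of the unadjusted test, to 80.5%, 80.9% and 81.5%.

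**Conclusion.** The mismatch between design and stated analysis is real, and its consequence is small and conditional. If the factors explain 2% to 10% of the variance the model otherwise leaves, type I error falls to between 4.8% and 3.9%, and 0.5 to 2.7 points of power are forgone. If they act only through baseline severity, essentially nothing is forgone.

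A reader might infer that the trial is underpowered, or that its standard errors are certainly wrong. The documents support neither. The sample size was derived without covariate adjustment, and on that calculation power without the factors stays between 80.3% and 82.9% for R² from 0 to 0.20. The omission does not bias the randomised comparison and does not inflate type I error. What is lost is possible extra precision.

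The size rests on the assumed R² range. The split between models in the simulation also rests on the assumed stratum proportions, block sizes and within-stratum correlation, with no missing data.

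**What to change.** In {20a} and in the OSF plan:

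- add complex PTSD (yes/no) and gender, with the values recorded at randomisation, to the primary mixed model together with their interactions with time;
- add both as main effects to the complementary baseline-adjusted regression;
- carry the same terms to the mirrored secondary models.

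If the sponsor prefers to leave the factors out, state the reason.

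The cost is a sentence or two and about 8 parameters in the mixed model, which is trivial at about 258 analysed participants. Both variables must already exist, because allocation depends on them. Timing matters more: according to Trial status, analysis begins once all primary-endpoint data are in, and inclusion is expected to run to August 2026. A change recorded before that analysis is prespecified. The same change made after results are seen would be open to challenge.

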#### Secondary outcomes and analyses

Unless stated otherwise, analyses mirror the primary modelling strategy: continuous outcomes will be analyzed with linear mixed-effects models using all available observations and yielding unbiased estimates under MAR/MCAR. Binary (and ordinal) outcomes will be analyzed with mixed-effects logistic (or cumulative-logit) models; cross-sectional categorical comparisons will use *χ*^2^ or Fisher’s exact tests as appropriate. Effect sizes will be reported as model-based standardized mean differences (Cohen’s *d*) for continuous outcomes and odds ratios for binary outcomes, each with 95% CIs. All secondary analyses are exploratory and *p*-values are nominal (no additional multiplicity adjustment).

#### Health-economic evaluation

A within-trial cost-effectiveness and cost-utility analysis will compare HOPE with the control at each assessment. QALYs will be derived from AQoL-6D using general-population tariffs. Costs will be estimated from a healthcare-provider perspective (intervention costs), a healthcare-system perspective, and a societal perspective using clinic resource use and TIC-P data. Results will be presented as incremental cost-effectiveness ratios (ICERs), with uncertainty characterized via non-parametric bootstrapping, cost-effectiveness planes, and cost-effectiveness acceptability curves across willingness-to-pay thresholds.

The full statistical analysis plan is uploaded on OSF: https://osf.io/dsg9p/.

### Interim analyses {21b}

Interim analysis of the results will be conducted twice during the study by an independent statistician: once when approximately one-third of the participants have completed the 1-month follow-up and again when approximately two-thirds of the participants have completed the 1-month follow-up. The purpose is safety monitoring, with emphasis on adverse events, serious adverse events, and withdrawals due to adverse events (frequency, severity, relatedness, and any between-arm imbalances). Unblinding will occur if required to evaluate a potential safety signal.

### Methods for additional analyses (e.g., subgroup analyses) {20b}

We will explore differences in treatment effects by gender in a subgroup analysis by including an interaction term between treatment arm and gender. Exploratory mediation will evaluate whether change in emotional responding, adherence, post-traumatic cognitions, avoidance, and alliance mediates treatment effects on CAPS-5. Moderation by baseline demographics and clinical history (e.g., PTSD/CPTSD severity, trauma type and timing, childhood adversity, comorbidity, perceived threat, education, employment, credibility/alliance) will be tested via treatment × covariate interactions; for prognostic models of CAPS-5 response, logistic regression will be used with model calibration assessed by Hosmer–Lemeshow and calibration plots.

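### Credibility and alliance are listed as baseline moderators but are measured after randomisation, and a change in alliance cannot be formed from a single WAI-SR

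*Protocol article*

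**What the plan says.** The additional-analyses section {20b} of the protocol article contains two plans that matter here.

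- **Mediation.** "Exploratory mediation will evaluate whether change in emotional responding, adherence, post-traumatic cognitions, avoidance, and alliance mediates treatment effects on CAPS-5".
- **Moderation.** The list is introduced as "Moderation by baseline demographics and clinical history", and its examples end with "perceived threat, education, employment, credibility/alliance) will be tested via treatment × covariate interactions".

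The measurement times are in the footnotes to Table 2 (Participant timeline {13}).

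- **Credibility:** "CEQ is administered after the first module in each treatment format".
- **Alliance:** "WAI-SR is administered at start of the third treatment week in each treatment format".
- **Distress ratings:** "SUD rating will only be collected in the HOPE group each time digital worksheets for exposure are filled in".

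Sequence generation {16a} places randomisation after eligibility and baseline assessment, so before either programme starts. Neither the outcomes section {12} nor the table gives a second occasion for the CEQ or the WAI-SR. Objectives {7} include processes of change and predictors of outcome, and the abstract counts mediators of change among the secondary outcomes. The mediation is labelled exploratory, as are all secondary analyses.

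**The concern.** A moderator analysis asks whether the treatment effect differs between kinds of patients, where the kind is fixed before treatment. Randomisation then makes the arms comparable at each level of the moderator. This fails for a variable measured after treatment has begun. Credibility after module 1 and alliance in week 3 are both ratings of the allocated programme and its therapist. Patients in HOPE with high alliance need not resemble patients in control with high alliance. If alliance picks up prognosis or early improvement more strongly in one arm, the interaction term differs from zero even when every patient has the same treatment benefit.

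The mediation problem is simpler. A change needs two measurements, and the schedule supplies one.

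What is at stake is the reading of exploratory results. A spurious interaction could be reported as evidence on who benefits from digital exposure, and one named mediation analysis could not be run as described.

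**Working it through.** **Step 1. Set the variables against the schedule.**

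| Variable | Role in {20b} | Measured | Consequence |
|---|---|---|---|
| Credibility (CEQ) | moderator, listed as baseline | once, after module 1, both arms | post-randomisation |
| Alliance (WAI-SR) | moderator, listed as baseline | once, start of week 3, both arms | post-randomisation |
| Alliance (WAI-SR) | mediator, as a change | same single occasion | level available, change not |
| Adherence | mediator | modules, messages and therapist time for each participant (Treatment variables) | estimable as a level |
| Demographics, PTSD and complex PTSD severity, trauma history | moderators | before treatment by nature | no timing problem |

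**Step 2. Sample size for the illustration.** The article gives no figure for these analyses, so I take its sample size. With d = 0.35, two-sided alpha 0.05 and 80% power, the two-sample t-test calculation gives 129.1 per arm, matching the stated 129. Allowing for 10% attrition, 129 / 0.90 = 143.3, which the article states as 143 per arm, 286 in total.

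**Step 3. What the interaction estimates when there is no moderation.** Assume an unmeasured prognostic factor U (SD 1), with T the arm (1 = HOPE):

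- outcome: Y = -0.35 T - b U + error, the same benefit for everyone;
- alliance: M = a T + k U + error (SD 1), with k allowed to differ by arm.

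Within an arm, the slope of Y on M is -b k / (k² + 1). The interaction is the HOPE slope minus the control slope. With b = 0.5 and k = 0.5 in HOPE, the HOPE slope is -0.25 / 1.25 = -0.200.

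- Control k = 0.5: control slope -0.200, interaction 0.
- Control k = 0.25: control slope -0.125 / 1.0625 = -0.118, interaction -0.082.
- Control k = 0: control slope 0, interaction -0.200.

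The true interaction is zero in all three cases.

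**Step 4. How often the test rejects at a nominal 5%.** Setting A has 129 per arm, b = 0.5 and 2,000 simulated trials per case, with the arm shifting alliance by a = 0, 0.3 or 0.5. Setting B has 143 per arm and b = 0.6.

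| Relation of alliance to U in control | Setting A | Setting B |
|---|---|---|
| same as in HOPE | 5.5-6% | about 5% |
| half as strong | 10-12% | about 14-15% |
| none (HOPE only) | about 39% | about 57% |

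The mean simulated interactions in setting A (about 0, -0.082 and -0.199) agree with step 3. The Monte Carlo standard error near 5% with 2,000 trials is √(0.05 × 0.95 / 2000) = 0.5 percentage points.

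**Step 5. The arm coefficient in the same model.** Even with equal slopes, adjusting for a variable that the arm shifts moves the arm coefficient. With a = 0.5 and slope -0.20, it becomes -0.35 - (-0.20 × 0.5) = -0.25. The simulation gives -0.254. The coefficient from such a model should not be read as the treatment effect.

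**The case against.** Several objections have force.

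- **The change wording may be loose.** Change may be meant to govern only the first item in the list. Adherence, the next item, has no baseline from which to form a change either. This is possible, so the point is put as the natural reading. The week-3 level is available in both arms and is usable. The text should say that this is what is meant.
- **The inputs are assumed.** Nothing in the article says that alliance tracks prognosis unequally by arm. Login schedule and response times are the same in both arms, and the same clinicians deliver both. This makes large inequality less likely but does not exclude it, since the content differs. With control slopes close to those in HOPE (0.4 against 0.3, or 0.5 against 0.4), rejection is only about 6-7%.
- **Alliance as both mediator and effect modifier is not an error in itself.** A mediation model may contain a treatment-by-mediator interaction. The error is treating alliance as a baseline covariate.
- **The analyses are exploratory.** This limits the claims, but it does not make a week-3 rating a baseline variable.

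A reader might also infer more than the article supports. One inference is that emotional responding cannot be studied as a mediator because distress ratings exist only in HOPE. That follows only if emotional responding means those ratings, and the article never says so. Another is that post-traumatic cognitions and avoidance have no instrument. Table 2 does not show everything that is collected, PCL-5 items gathered weekly in both arms could serve, and the full analysis plan on OSF is not at hand. No claim is made on either point.

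**Conclusion.** The concern holds in a limited form. Two statements in {20b} conflict with the article's own schedule: credibility and alliance are not baseline variables, and a change in alliance cannot be formed from one WAI-SR. Both follow from the text and need no assumption beyond the natural reading of the mediation sentence.

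The size of the moderation problem does rest on assumptions. False positives are about 5% if alliance relates to outcome equally in both arms, about 10-15% if the relation is half as strong in control, and about 39-57% if it exists only in HOPE. The last range is an unfavourable extreme and should not be taken as the expected error rate. Bias is a risk here, not a certainty.

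It would go too far to conclude that the mediation and moderation plan as a whole cannot be estimated or is biased. Adherence as a level and the true baseline moderators have no such problem. The primary CAPS-5 comparison and the sample size are unaffected. The correction is worth making because processes of change and predictors are stated objectives.

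**What to change.** Reconcile {20b} with Table 2:

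1. Remove credibility and alliance from the baseline moderator list, or report them only as post-randomisation process variables without reading an interaction as effect modification.
2. State that alliance enters the mediation model as its week-3 level.
3. If emotional responding is to be measured by the distress ratings, describe that analysis as a within-HOPE process description, since no between-arm path can be estimated from ratings in one arm.

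The cost is a change of wording in the protocol and the OSF plan, with no new data, and fewer exploratory moderator and mediator claims. The article already commits to disclosing modifications on OSF and the trial registry. It expects inclusion to end in August 2026, with analysis to begin once all primary-endpoint data are in. The change should be registered before that analysis starts.
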